### 2.8. Statistical Analysis

The statistical analysis will be conducted through the Statistical Package for the Social Sciences software (SPSS, Version 25, IBM SPSS, Armonk, NY, USA).

The characteristics of the study participants will be presented as the mean (standard deviation) and proportions for continuous and categorical variables, respectively. We will carry out an intention-to-treat (all participants), and a per-protocol analysis (individuals who complete the program).

Intention-to-treat analysis: All of the randomised participants will be considered for the analysis in their relevant group. Missing data will be imputed through multiple imputations. Repeated measures analyses of covariance (ANCOVA) adjusted by age and baseline outcomes will be applied to analyse the intervention effects on the different dependent variables. The baseline outcomes will be applied as a covariate for all of the dependent variables’ pre–post-comparisons in order to avoid the bias of possible differences between the groups in the initial outcomes. The effect sizes (95% confidence interval) and differences for each variable concerning the time and the group × time interaction will be calculated. The alpha level will be set at *p* < 0.05. The data imputation for the sensitivity analyses will be conducted on patients who presented data at the baseline, and who completed the study, in order to avoid estimation bias.

Per-protocol analysis: The analyses previously described will be carried out but considering only those participants who attended at least 75% of the program sessions.

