### 2.3. Sample Size

The sample size was estimated based on the Time Up and Go (TUG) test results in older people, a test which is considered valid and reliable for this population [43,44]. Thus, accepting a risk alpha of 0.05 and a risk beta of 0.2 in a bilateral contrast, a total of 44 individuals (22 both in the experimental and control group) are needed in order to find a difference equal to or higher than 0.97 units. A common standard deviation of 1.3 and a correlation coefficient between the baseline and end-line measurement of 0.7 are assumed [45]. A loss of follow-up rate of 20% is predicted.

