#### 2.6.3. Control Group

Participants will perform the McTP program without the tDCS stimulation. 

Both the experimental and control groups will participate in the initial, mid-term and final evaluations.

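### Section 2.8 names only time and group × time as effects to be calculated and does not say which of the three visits are levels of time, so the named test matches the week-12 effect under only one of three codings

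*Protocol article*

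**What the plan says.** Section 2.8 fixes the model: "Repeated measures analyses of covariance (ANCOVA) adjusted by age and baseline outcomes will be applied to analyse the intervention effects". It adds that the baseline value is a covariate in the pre–post comparisons of every dependent variable. It then lists what is to be estimated: "The effect sizes (95% confidence interval) and differences for each variable concerning the time and the group" (the sentence goes on to make this last term the interaction of group with time). It names no between-group term and no adjusted contrast at a given visit.

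There are three assessments. Section 2.6.3 says "Both the experimental and control groups will participate in the initial, mid-term and final evaluations", and Table 2 places balance at weeks 0, 6 and 12. Section 2.8 does not say how the week-6 visit enters the model, or whether week 0 is a level of time as well as a covariate.

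Section 2.3 sizes the trial on one TUG difference, with two-sided alpha 0.05 and power 0.80. Its result is that "a total of 44 individuals (22 both in the experimental and control group) are needed". The stated purpose of that number is to "find a difference equal to or higher than 0.97 units". On variability it says "A common standard deviation of 1.3 and a correlation coefficient between the baseline and end-line measurement of 0.7 are assumed", and it allows for 20% of participants being lost. The design target is therefore a difference between arms at the end of the programme.

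**The concern.** What group × time means in a repeated-measures ANCOVA depends on the levels of time, and the article leaves these open. Three codings fit its wording.

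- **A. Levels are weeks 6 and 12, with baseline as covariate only.** The treatment effect is the group term, or the group contrast at week 12. Group × time asks only whether the effect differs between weeks 6 and 12.
- **B. Levels are weeks 0, 6 and 12, with baseline also a covariate.** Baseline is then both an outcome and a covariate. Group × time is a 2-df omnibus test of any departure at week 6 or week 12.
- **C. Levels are weeks 0 and 12, with baseline as covariate.** Group × time is the adjusted week-12 difference.

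The interaction is the only term involving treatment that the article names. Under A, a real and sustained benefit could be reported as a null result. Under B, a positive result would not show that the benefit is present at week 12. Leaving the coding open also allows it to be chosen after the data are seen.

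**Working it through.** **Inputs from Section 2.3:** difference 0.97 (taken as seconds, since TUG is a time), SD 1.3, baseline-to-end-line correlation 0.7, two-sided alpha 0.05, power 0.80, 20% loss, 22 per arm.

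**Assumed, not in the document:** week 0–6 correlation 0.7; week 6–12 correlation 0.7 or 0.8; 17 analysed per arm (the size before inflation for loss) or 22 (all randomised, treated as fully observed).

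**1. Reproduce the sample size.**
- SD of change = 1.3 × √(2 × (1 − 0.7)) = 1.007.
- n per arm = 2 × (1.96 + 0.842)² × 1.007² / 0.97² = 16.9, so 17.
- With 20% loss, 17 / 0.8 = 21.25, so 22 per arm and 44 in total. This matches the plan.

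The trial was thus sized on a two-point change, week 0 to week 12.

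**2. What group × time estimates.** Write the effect at week 6 as δ6 and at week 12 as δ12.
- A: δ12 − δ6. For a steady benefit this is 0.97 − 0.97 = 0, so the rejection rate equals alpha whatever the sample size or correlation.
- B: the pair (δ6, δ12) tested jointly on 2 df.
- C: δ12. Subtracting baseline from the week-12 value while baseline is a covariate changes only the baseline slope, by −1. The group coefficient and its test are those of the week-12 ANCOVA.

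**3. Power by simulation** (6,000 runs per scenario, baseline and age as covariates). For B, the two figures are the multivariate test and the univariate test assuming sphericity.

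| Per arm | Week 6–12 correlation | Effect at weeks 6, 12 | A: group × time | A: group term | B: group × time | Week-12 ANCOVA (= C) |
|---|---|---|---|---|---|---|
| 17 | 0.7 | 0.97, 0.97 | 0.048 | 0.926 | 0.857 / 0.851 | 0.818 |
| 17 | 0.8 | 0.97, 0.97 | 0.049 | 0.884 | 0.796 / 0.855 | 0.807 |
| 22 | 0.7 | 0.97, 0.97 | 0.048 | 0.975 | 0.940 / 0.934 | 0.910 |
| 22 | 0.8 | 0.97, 0.97 | 0.052 | 0.955 | 0.906 / 0.939 | 0.910 |
| 17 | 0.7 | 0.485, 0.97 | 0.271 | 0.721 | 0.712 / 0.715 | 0.810 |
| 17 | 0.8 | 0.485, 0.97 | 0.363 | 0.658 | 0.712 / 0.752 | 0.813 |
| 22 | 0.7 | 0.485, 0.97 | 0.329 | 0.836 | 0.837 / 0.838 | 0.906 |
| 22 | 0.8 | 0.485, 0.97 | 0.462 | 0.785 | 0.835 / 0.863 | 0.902 |

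With no effect at either visit, every test rejects in about 5% of runs (0.045–0.058).

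**4. Specificity under B.** If the effect is 0.97 at week 6 and zero at week 12, the omnibus interaction is significant in about 79–96% of trials. The week-12 contrast is significant in about 4–6%.

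**5. Does the sample size support a week-12 ANCOVA?** Residual SD = 1.3 × √(1 − 0.7²) = 0.928. Then n = 2 × (1.96 + 0.842)² × 0.928² / 0.97² = 14.4, so 15 per arm; 15 / 0.8 = 18.75, so 19 with loss. The planned 22 per arm covers this.

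**The case against.** The strongest reply is that the text already points to coding C. It speaks of pre–post comparisons, and the sample size reproduces exactly from a two-point change score. If that is what is meant, group × time is the week-12 ANCOVA effect and nothing is lost. This stands as a plausible intention. But the same paragraph specifies a repeated-measures model in a three-visit trial, and nothing confines it to two visits.

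A reader might infer that the plan will miss a sustained benefit. The documents do not support that. It needs coding A, which is nowhere stated, and an effect already complete at week 6 and flat afterwards. Section 2.6.1 describes gradually increasing intensity, volume and complexity, so a flat effect is only one scenario. A reader might also infer that entering baseline twice under B invalidates the test. It does not: type I error stays near 5%, and power for a steady benefit is about 80–94%. The week-6-only case in step 4 is likewise an extreme pattern, used to show what the test cannot distinguish.

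Nor does the article say that nothing beyond time and group × time will be reported; it names those two and is silent on the rest. Coding detail can be left to an analysis plan that is not shown. What remains is that the article itself fixes which effects are calculated, and that choice fits the trial's question under one coding of three.

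**Conclusion.** The point holds as a defect of specification that should be corrected, not as proof that the analysis will give a wrong answer. The named interaction equals the week-12 treatment effect only if time has the two levels week 0 and week 12. With weeks 6 and 12 as levels, a steady 0.97 benefit is detected at about 5%, and one growing from 0.485 to 0.97 at about 27–46%, while the week-12 contrast has about 81–91% in either case. With three levels, power for a steady benefit is largely kept, but a significant result does not locate the effect at week 12.

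The 5% figure for a steady effect follows from the definition of the contrast. The other figures rest on the assumed week 0–6 and week 6–12 correlations and on 17–22 analysed per arm. The sample size of 44 is not called into question by this point.

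**What to change.** In Section 2.8, name as the primary test the between-group difference in TUG at week 12, adjusted for baseline TUG and age, with its 95% CI. Either of two models gives this: an ANCOVA of the week-12 value, or a mixed model on weeks 6 and 12 from which the week-12 group contrast is read. State that week 0 enters only as a covariate and not as a level of time. Report the week-6 difference and group × time as secondary.

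This costs a few lines. It needs no new data, no other software and no more participants. The small downside is that the interaction is no longer the headline test.

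### The imputation rule for the sensitivity analyses leaves out dropouts, so those analyses cannot test the intention-to-treat result, and the reason given for the rule is wrong

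*Protocol article*

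**What the plan says.** The intention-to-treat paragraph of section 2.8 opens without restriction: "All of the randomised participants will be considered for the analysis in their relevant group", followed by "Missing data will be imputed through multiple imputations". After describing the ANCOVA, it closes with a narrower rule: the imputation behind the sensitivity analyses "will be conducted on patients who presented data at the baseline, and who completed the study, in order to avoid estimation bias". The article does not say elsewhere what the sensitivity analyses are.

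Section 2.8 also plans a per-protocol analysis. It first describes this as an analysis of people who complete the programme, and later as one "considering only those participants who attended at least 75% of the program sessions".

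On expected dropout, section 2.3 says: "A loss of follow-up rate of 20% is predicted". Assessments are at weeks 0, 6 and 12 (Table 2). Randomisation follows the initial assessment (section 2.4), so nearly every randomised participant should have baseline data. Of the two conditions in the closing sentence, completion is the one that removes people.

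**The concern.** A sensitivity analysis for missing data should show how far the main result depends on what is assumed about people whose outcome was not seen. Here those people are the dropouts, and the rule removes them before imputation starts. What remains is close to a complete-case analysis at week 12 and overlaps heavily with the per-protocol analysis.

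The stated justification also points the wrong way. Completion happens after randomisation, so selecting on it gives up the comparability that randomisation provided. If leaving depends on both the arm and how a participant is doing after baseline, the completer comparison is biased.

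That is plausible in this trial. Participants and session leaders know the allocation (section 2.4), only the experimental arm wears the device, and the control arm has no sham (sections 2.6.2 and 2.6.3). Agreement between such a check and the main analysis would be read as robustness without being evidence of it.

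**Working it through.** **1. The plan's own sample size, to confirm the loss it expects.** Inputs from section 2.3: difference 0.97, SD 1.3, correlation 0.7, two-sided alpha 0.05, power 80%, loss 20%.

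- SD of change = 1.3 × √(2 × (1 − 0.7)) = 1.007.
- n per arm = 2 × (1.007 × (1.960 + 0.842) / 0.97)² = 16.9, rounded up to 17.
- With 20% loss: 17 / 0.8 = 21.25, rounded up to 22 per arm, or 44 in total.

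This matches the stated 44, so the design already has the 20% loss built in. Nothing in this point changes the sample size.

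**2. Who is left out.** The abstract plans 46 participants, 23 per arm. Expected dropouts are 0.20 × 46 = 9.2, about 9. Imputation under the closing sentence covers 0.80 × 46 = 36.8, about 37. Imputation under the opening sentences covers all 46. I take completing the study to mean having the final assessment; the article does not define it. On that meaning, completers could still need imputation for a missed week-6 visit or a questionnaire gap, but hardly at all for week 12.

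**3. Can a completer analysis be biased, and by how much?** The illustration uses 23 per arm, SD 1.3, no true effect and 5 lost per arm, leaving 18. The correlation is 0.7 between every pair of visits; the plan gives 0.7 only for baseline to end, so its use for week 6 is an assumption. Week-12 TUG is compared between completers by ANCOVA on baseline. A negative value favours tDCS.

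| Who is lost | Bias (s) | Type I error |
|---|---|---|
| tDCS: slowest at week 6; control: random | −0.10 to −0.12 (three runs of 8,000 to 10,000 replicates) | 6.3 to 6.5% |
| Slowest at week 6 in both arms | −0.003 | 5.4% |
| Random in both arms | −0.003 | 4.6% |
| tDCS: slowest at baseline | −0.004 | 4.7% |

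The last three rows come from 8,000 replicates. The simulation error of a 5% rate is then √(0.05 × 0.95 / 8,000) = 0.24 percentage points, so these rows do not differ clearly from 5% or from zero bias.

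**4. Hand check of the first row.** Losing the slowest 5 of 23 (21.7%) cuts the normal distribution at z = 0.781, where the density is 0.294.

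- Week-6 mean of those kept shifts by −0.294 / 0.783 = −0.376 SD, or −0.488 s.
- Baseline and week-12 means each shift by 0.7 × (−0.488) = −0.342 s.
- ANCOVA corrects for the baseline shift using the fitted slope b, leaving a bias of −0.342 × (1 − b).
- With b = 0.7 the bias is −0.10 s. Selection lowers the pooled slope: the baseline variance in the selected arm becomes 0.787 and its covariance with week 12 becomes 0.487 (in SD² units), so b = (0.700 + 0.487) / (1 + 0.787) = 0.664 and the bias is −0.115 s.

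This agrees with the simulation. By symmetry, losing the fastest instead of the slowest reverses the sign.

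**5. Does imputing for dropouts help?** In the first scenario, regression imputation within arm, using baseline and week 6, gave a mean within 0.01 s of zero in two separate runs. Dropout there depends on an observed value, the week-6 time, and the imputation uses it.

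**The case against.** The strongest reply is that the closing sentence governs only the sensitivity analyses. The two opening sentences place no limit on who is imputed, so the main analysis can cover all 46, and a supportive analysis may use a different set. This stands. A reader might infer that the paragraph contradicts its own intention-to-treat statement, but the wording does not support that. What remains is ambiguity: the sentence sits in the intention-to-treat paragraph, no sensitivity analysis is described, and an analyst could take it as the imputation set for the whole trial.

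A second reply is that the bias depends on a chosen scenario. This also stands. The protocol gives one overall loss rate and nothing on who leaves. The bias needs outcome-related loss that differs between the arms, and even then about 0.11 s is only about a third of the estimator's SD of 0.31 s. A reader might infer that the check would favour tDCS, but the documents do not support a direction.

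A third reply is that the choice of imputation model and sensitivity method commonly belongs in an analysis plan that is not shown. That is fair for the details, and imputing separately by arm is debatable with about 18 completers per arm. It does not excuse the sentence itself, which fixes a rule and gives a wrong reason for it.

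Finally, the overlap with the per-protocol analysis is large but not complete: someone who attended under 75% of sessions may still return for the final assessment.

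**Conclusion.** The point holds for the sensitivity analyses. As written, they impute nothing for about 9 of 46 expected dropouts, come close to a completer analysis at week 12, and cannot show whether the intention-to-treat result survives other assumptions about those who left. The justification is incorrect: restricting to completers does not protect against bias and can introduce it in either direction.

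The size is modest and conditional. Under one-sided selective loss it is about 0.1 s, which is 10 to 12% of the 0.97 target (0.10 / 0.97 and 0.12 / 0.97), with type I error 6.3 to 6.5%. Under random or equally selective loss it is about zero. These figures assume the plan's SD and correlation, the same correlation at week 6, and 5 losses per arm. They show what can happen and are not a forecast. The primary result is affected only if the closing sentence is applied to the main analysis.

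**What to change.** In section 2.8:

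1. Delete the completer restriction and its rationale.
2. State that multiple imputation covers all randomised participants with baseline data, whether or not they completed, using baseline value, week-6 value and age.
3. If a completer analysis is wanted, name it separately and label it supportive.
4. Make the sensitivity analysis vary the assumption about dropouts' missing week-12 outcomes, for example by delta-adjusted or reference-based imputation. Either would serve, and the details can go in the analysis plan.

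The cost is two sentences and a little programming, with no change to sample size, visits or data collection. The change should be made before anyone sees outcome data by arm.

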## 3. Discussion

This study the efficacy of Halo-implemented McTP to improve balance, in order to improve postural stability to decrease falls. Moreover, it presents direct measures of safety and applicability (Halo Sport) for its applications in community-dwelling older adults, providing data about their effectiveness in the prevention of falls, functional capacity, and quality of life. This is a novel approach starting from an integrative perspective, including elements that combine physical motivation and cortical stimulation.

The high incidence of falls in the elderly [70] underlines the need to boost the design of prevention programs. The impact of frailty in older people constitutes a prominent health problem. The decline in muscle mass associated with age has a negative influence on strength and movement capacity, leading to a reduced quality of life [71]. Muscle strength and balance are, therefore, key components of physical activity programs to reduce the fall risk in the elderly [72]. This program complies with the recommendations from the WHO [22] and the ACSM [23] by taking into account strength, cardiorespiratory endurance, balance and flexibility.

In addition, the results obtained with tDCS techniques—which have shown an improvement in motor activity, locomotion, mobility and gait speed [73,74,75]—are in the same line. If the effectiveness of the Halo-implemented McTP on motor learning and improvement of balance, fitness and lower-limb strength is demonstrated, conventional training programmes could be implemented with this kind of device to decrease the risk of falls. Furthermore, it would have an impact on the sociosanitary area through its possible implementation in primary care, rehabilitation and care centres in order to reduce the number of falls. If positive outcomes are obtained, the intervention proposed could be offered as an alternative or complementary tool for health professionals to enhance the quality of life of the elderly, and to minimise the economic impact of falls.

## 4. Conclusions

This trial will research Halo-implemented McTP’s efficacy, safety and applicability to increase balance in order to prevent falls in community-dwelling older adults. We hypothesise that the combined program (McTP-tDCS) will be more effective than the McTP carried out in isolation.

## Figures and Tables

**Table 1 biology-11-00290-t001:** Examples of the activities and exercises performed according to the physical abilities in the multi-component training programme.

Physical Ability	Examples
Balance	Exercises on one foot, tandem or semi-tandem position. Exercises in movement walking with heel to toe support. Line walking. Multidirectional movements with extra weights. Altering the base of support. Modified Tai Chi exercises.
Strength	Free weights. weight-bearing exercises. Machines exercises. Pilates.
Cardiorespiratory endurance	Walking indoors and outdoors. Treadmill walking. Stationary cling. Climbing steps/stairs.
Flexibility	Stretches. Yoga.

**Table 2 biology-11-00290-t002:** Schedule of the evaluations in the experimental and control groups.

Measures	Week 0	Week 6	Week 12
Sociodemographic data	√		
Balance	√	√	√
Number of falls (a) last year (b) last 6 and (c) 3 months	√	√	√
Physical fitness	√	√	√
Fall Risk	√	√	√
Fear of falling	√	√	√
Health-related quality of life	√	√	√
Cognitive function	√	√	√
Security	√		√
Applicability	√		√

## Data Availability

The datasets used during the current study are available from the corresponding authors on reasonable request.
